## 2. Per Protocol Set (PPS)

A group of subjects (mother, fetus/infant) excluding subjects showing deviations associated with protocol treatment and related to prohibited drugs from FAS.

## 3. Safety analysis target population

All subject populations (mother, fetus/infant) who received at least one protocol treatment.

# 14.2 STATISTICAL ANALYSIS

## 14.2.1 SUBJECT BACKGROUND

| Background information/primary outcome/secondary outcomes                                                                                                                                                                                                                                                                                                                                                                                                                                   | FAS/PPS                      | Statistics                                                                                                                                                                      |
|---------------------------------------------------------------------------------------------------------------------------------------------------------------------------------------------------------------------------------------------------------------------------------------------------------------------------------------------------------------------------------------------------------------------------------------------------------------------------------------------|------------------------------|---------------------------------------------------------------------------------------------------------------------------------------------------------------------------------|
| Background information
Age, ethnicity, blood type (ABO, Rh), smoking habit, day of consent, gestational weeks and days at entry into this trial, gravidity, parity, therapy for sterility, body weight (pre-pregnancy, on giving consent), basic complications, any past obstetrical histories, presence/absence of allergy (food, drugs), onset date (gestational weeks and days) of pPROM, findings of pPROM (presence/absence of leak alone, pooling alone, or both leak and pooling) | Mainly FAS, followed by PPS. | Summary statistics (mean, standard deviation, minimum value, median, maximum value)* for continuous variables, and the numbers, frequencies, and 95% CI for discrete variables. |

Subject background information will be summarized in the FAS, PPS, and safety analysis populations. For discrete data, frequencies and proportions are calculated for each group; for continuous data, summary statistics (mean, standard deviation, minimum, median, maximum) are calculated for each group.

## 14.2.2 ANALYSIS OF PRIMARY OUTCOME

| Background information/primary outcome/secondary outcomes                                                             | FAS/PPS                      | Statistics                                                                                                                                                                                                                                                                                                                                                                                         |
|-----------------------------------------------------------------------------------------------------------------------|------------------------------|----------------------------------------------------------------------------------------------------------------------------------------------------------------------------------------------------------------------------------------------------------------------------------------------------------------------------------------------------------------------------------------------------|
| Primary outcome
Incidence rate of either moderate/severe BPD 36 or IUFD at or less than 36 weeks 0 days | Mainly FAS, followed by PPS. | Intervention group vs. control group
(1) The difference in crude rate, 95% CI. (2) adjusted risk difference and 95% CI by the Mantel-Haenszel method, adjusted for gestational weeks at onset of pPROM (22 weeks 0 days to 23 weeks 6 days, 24 weeks 0 days to 27 weeks 6 days) and institute (institute where early caffeine will be used, institute where early caffeine will not be used)**. |

In analyses using FAS, all subjects with missing primary outcome will be treated as having "moderate or greater BPD36 or occurrence of death in child up to 36 weeks PMA" for any reason. In analyses using the PPS, subjects with missing primary endpoints will be excluded from the analysis.

A two-tailed test will be conducted with the null hypothesis that "the proportion of moderate or higher BPD36 or child deaths up to 36 weeks PMA is equal between groups" and the alternative hypothesis that "the proportion of moderate or higher BPD36 or child deaths up to 36 weeks PMA is different between groups." The p-value will be calculated by testing the difference in proportions. The significance level is set at 0.05.

Calculate the percentage of the primary outcome and its 95% confidence interval for each of the intervention and control groups. In addition, the difference in proportions between groups and their 95% confidence intervals will be calculated. This will be the main analysis. The Mantel-Haenszel adjusted risk difference and its 95% confidence interval will also be calculated, adjusted for week of pregnancy (22 weeks 0 days to 23 weeks 6 days, 24 weeks 0 days to 27 weeks 6 days) and facility (early caffeine-using facility, early caffeine-unused facility) as stratification factors.

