# As for infants with birth at gestational ages <32 weeks PMA, the assessment of BPD36 should be performed at 36 weeks PMA or discharge to home, whichever comes first. As for infants with birth at gestational ages ≥32 weeks PMA, the assessment of BPD36 should be performed at ≥28 and <56 days postnatal age or discharge to home, whichever comes first.

a. CI or SI should investigate serious adverse events of the infant within 3 days after the cancelation of participation in this trial.

b. CI or SI should investigate the neonatal sex, birth weight (g), birth height (cm), head circumference at birth (cm), and presence/absence of small for dates, light for dates, large for dates, and heavy for dates.

c. The Apgar score should be recorded at 1 and 5 minutes after delivery.

d. The sampling of blood for the blood gas test is acceptable from either artery, vein, or capillary vessels.

e. CI or SI should not take biological specimens from the infant if the mother becomes complicated with COVID-19 infection.

f. CI or SI should investigate the presence/absence of intracranial hemorrhage (ICH), periventricular leukomalacia (PVL), respiratory distress syndrome (RDS), meconium aspiration syndrome (MAS), transient tachypnea in newborns (TTN), prolonged pulmonary hypertension (PPH), sepsis, necrotizing enterocolitis (NEC), local intestinal perforation, symptomatic patent ductus arteriosus (PDA), subglottic stenosis, laryngomalacia, and other upper airway diseases. CI or SI should also investigate the presence/absence of surgery for the infant. If the infant has any surgeries, CI or SI should investigate the surgical procedure, day of surgery, aim of surgery, and execution of intubation for the surgery.

g. CI or SI should investigate oxygen administration, intravenous/intratracheal administration of steroid, nitrogen monoxide inhalation, surfactant administration, caffeine administration, and azithromycin (AZM) treatment.

h. CI or SI should investigate serious adverse events of infants from the termination of pregnancy to discharge of the infant (or day of cancelation of participation in the trial for the mother).

i. The hematological examination and blood biochemical test at the termination of pregnancy for the infant are possible using cord blood.

j. The examination of IgM is performed only at delivery.

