## 4.2 RANDOMIZATION

Allocation will be done by REDCap in the order of registration. REDCap will assign subjects (maternal and fetal) who meet all inclusion criteria to the intervention or control group 1:1 by stratified allocation. Because the incidence of BPD varies with the number of weeks of gestation at the onset of pPROM (22 weeks 0 days to 23 weeks 6 days and 24 weeks 0 days to 27 weeks 6 days) and facility (early caffeine-using facility or early caffeine-unused facility), stratification factors will be used at the time of randomization. The implementing facility will be surveyed prior to participation to determine if the facility is an early caffeine using facility.

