## 5.2 TARGET NUMBER OF CASES

### 5.2.1 TARGET NUMBER OF CASES

Target number of cases: 50 in the test group and 50 in the control group (total 100 cases)

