The median number of weeks of gestational duration for pregnant women with pPROM is 2 weeks. Based on the annual number of deliveries, the number of births by week, and the percentage of pPROM, we can estimate that 1,200 newborns per year are born at <30 weeks to pregnant women with pPROM complications. In the 20 regional and comprehensive perinatal centers scheduled to participate in this study, the number of cases is estimated to be approximately 200 per year over a 2-year period. Assuming that 50% of the patients meet the eligibility criteria for this study and consent is obtained, 100 patients can be enrolled over a two-year period, and from the viewpoint of feasibility, the target number of cases for this study was set at 100. Under a two-tailed test and a significance level of 5%, the power of detection ranged from 0.516 to 0.995 when the assumed BPD36 incidence rate in the intervention group was 18.0% to 40.0%, which is considered to guarantee a power of at least 0.5.

For reference, the power curve for the BPD36 incidence rates of 18.0% to 60.0% in the intervention group are shown below. In addition, the incidence rates in previous foreign and domestic studies and the study at Saga Hospital are indicated by red lines.

[figure not shown]

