#### (4) Administering oxygen to the child

If oxygen is administered to the infant and if oxygen is administered, the duration, oxygen concentration, oxygen flow rate, and inhaled oxygen concentration (if FiO2, oxygen mask, mouth oxygen blow down, or hood) by oxygen administration method will be surveyed and entered into the eCRF. If the neonate remains hospitalized at the 36 weeks 0 days PMA (or at the time of cancelation of participation in the trial), the neonate will be surveyed until discharge, if possible.

Time of implementation: at termination of pregnancy (at birth), day 3, day 7, day 28\*1, 36 weeks 0 days\*2, at discharge of the child

\*1: For children discharged by day 28, evaluation is performed at the 1-month check-up.

\*2: For children born at 32 or more weeks of gestation, evaluate at day 56 or at discharge from the hospital, whichever comes first.

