## 10 CANCELTION AND COMPLETION

### 10.1 CANCELTION OF PARTICIPATION IN THE TRIAL

If the subject fails to comply with all study schedules, including efficacy and safety assessments, as well as discontinues protocol treatment for the following reasons (1. to 3.), participation in this trial should be canceled. This situation is called “cancellation of participation in the trial”.

If the protocol treatment is canceled before it has actually started, no observations should be performed, and appropriate treatment should be given so that the subject is not disadvantaged in

normal practice.

1. When the subject withdraws consent to participate in the study.
2. When “disease, etc.” that may lead to death or death occurs.
3. In addition, when the investigator determines that the risk of participating in the trial outweighs the benefits.

Basis for setting

- 1: Set from an ethical point of view.
- 2 – 3: Established from the viewpoint of subject safety.

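### After cancellation of participation, BPD36 is not scheduled for the infant, and the FAS rule then scores the gap as BPD or death, so unequal cancellation shifts the main comparison

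*Protocol*

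**What the plan says.** **Scoring rule.** Protocol 14.2.2 says: "In analyses using FAS, all subjects with missing primary outcome will be treated as having" moderate or worse BPD36 or death, for any reason. The FAS is the primary population (14.1), and the crude difference in proportions is the main analysis. In the PPS, missing outcomes are dropped.

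**Cancellation.** Section 10.1 lists three reasons for which "participation in this trial should be canceled": withdrawal of consent, a fatal or potentially fatal trial-related disease, and an investigator's judgement that risk outweighs benefit. Notes k and l of Table 1.3-1 foresee cancellation because of adverse events.

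**What is collected afterwards.** In Tables 1.3-2 and 7.5-2 the cancellation column is marked for serious adverse events only, and the BPD36 row is blank there. Note a reads: "CI or SI should investigate serious adverse events of the infant within 3 days after the cancelation of participation in this trial". Note h ends infant SAE collection on the day the mother's participation is cancelled. Section 7.5.3 (3) and (4) point the other way for an infant who is in hospital at that time. Under item (4), on oxygen, "the neonate will be surveyed until discharge, if possible"; item (3) says the same of respiratory support.

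**Provisions that limit the problem.** Section 6.2.6 keeps women who only stop protocol treatment on the full schedule. Section 14.1 removes from the FAS treated subjects with no data after treatment.

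**The concern.** Read together, these sections let the primary outcome go uncollected for some infants and then count each such infant in the FAS as a failure. Scoring missing as failure is conservative in a single-arm study. In a two-arm comparison it is not: it penalises whichever arm has more missing outcomes, whatever happened to those infants. Treatment is open-label, so the woman and the investigator know the arm when a consent or risk-benefit decision is made. Blinded BPD adjudication does not help, because the committee has nothing to judge when no data were collected.

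Two things are at stake. The first is the between-arm difference, if cancellation is unequal. The second arises even when it is equal: both event rates rise and the difference between them shrinks. Estimating those rates to size a Phase III trial is part of the primary objective.

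**Working it through.** **Inputs from the protocol**
- 50 per arm (5.2.1), allocated "to the intervention or control group 1:1 by stratified allocation" (4.2).
- Two-sided test: "The significance level is set at 0.05" (14.2.2).
- Event rates of 60% for EM and 18% to 40% for AZM (5.2.2).

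**Input assumed.** The share *m* of an arm's FAS infants whose outcome is missing after cancellation. The protocol gives no figure, so 0% to 20% is used for illustration.

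**Step 1: reproduce the stated power.** Section 5.2.2 says: "Under a two-tailed test and a significance level of 5%, the power of detection ranged from 0.516 to 0.995". With pooled variance under the null, power = Φ[(d − 1.96·SE0)/SE1], where SE0 = √(2·p̄(1−p̄)/50) and SE1 = √((p1(1−p1)+p2(1−p2))/50).
- 60% v 40%: (0.20 − 1.96×0.1000)/0.0980 = 0.041, so power is 0.516.
- 60% v 18%: (0.42 − 1.96×0.0975)/0.0880 = 2.60, so power is 0.995.

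Both ends agree with the protocol.

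**Step 2: effect of the rule on one arm.** Observed rate = p + (1−p)·m. One missing infant in 50 adds (1−p)/50 to the expected rate. That is 0.8 points at p = 60% and 1.2 points at p = 40%.

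**Step 3: no true difference, unequal missingness.** Spurious difference = (1−p)·(difference in m). Rejection is the exact binomial probability for the pooled z-test, 50 per arm, two-sided 0.05.

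| Missing, arm 1 / arm 2 | True rate 60%: shift, rejection | True rate 40%: shift, rejection |
|---|---|---|
| 0% / 0% | 0 points, 5.2% | 0 points, 5.2% |
| 0% / 5% | 2 points, 5.7% | 3 points, 6.5% |
| 0% / 10% | 4 points, 7.1% | 6 points, 10.0% |
| 0% / 20% | 8 points, 13.2% | 12 points, 24.1% |
| 5% / 5% | 0 points, 5.1% | 0 points, 5.5% |

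The shift always favours the arm with fewer missing outcomes.

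**Step 4: true difference of 60% v 40%** (formula of step 1)
- 10% missing in both arms: observed 64% v 46%. (0.18 − 1.96×0.0995)/0.0979 = −0.153, so power is 0.439, against 0.516 with none missing.
- 10% missing in EM only: observed 64% v 40%, power 0.676.
- 10% missing in AZM only: observed 60% v 46%, power 0.287.

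**Step 5: Phase III sizing, if the imputed rates were carried forward.** With 5% missing in both arms, 60% v 40% is observed as 62% v 43%. The size for 80% power goes from 97 to 108 per arm.

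**The case against.** The strongest reply is that few women should reach this gap. A reader might infer that the endpoint absorbs maternal tolerability in general, because EM carries more infusions and tablets per day than AZM. The protocol does not support that. Under 6.2.6, a woman who stops treatment because infusions must be withheld after an adverse event, by her own wish, or on the physician's judgement stays in the trial on the full schedule. Only the narrower reasons in 10.1 remove her.

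A reader might also infer that every cancelled infant leaves BPD36 follow-up and is scored as an event. That is too strong as well. Where the 7.5.3 survey is done, BPD36 can often be derived, since it is defined by oxygen or respiratory support use. Treated subjects with no later data leave the FAS and are not imputed.

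These replies narrow the route but do not close it. The 7.5.3 survey is optional, names neither BPD36 nor the oxygen reduction test, does not cover a woman cancelled before delivery, and sits badly with the schedule tables.

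Three further replies have some force:
- **Size.** It rests on assumed missing shares, and modest shares give shifts well inside the sampling error of the difference (about ±1.96×0.098, or 19 points). This limits the urgency, but sampling error does not excuse an avoidable bias.
- **PPS.** It handles missing outcomes differently. But it also removes protocol deviators, so it does not isolate the effect of this rule.
- **Phase III.** Nothing says the imputed rates will be used for sizing, so step 5 is conditional. Details of imputation may properly sit in an analysis plan that is not shown here.

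**Conclusion.** The point stands in a limited form. The protocol leaves BPD36 unscheduled after cancellation under 10.1, contradicts itself on whether respiratory data continue, and scores each gap remaining in the FAS as BPD or death. Cancellation between Day 1 and delivery is the clearest exposure.

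The direction of the bias is certain: against the arm with more missing outcomes. Which arm that will be is unknown, and equal missingness creates no spurious difference. For an assumed imbalance of 5 to 20 points, with equal true rates of 40% to 60%, the shift is 2 to 12 points and two-sided rejection about 6% to 24%, against 5.2% with none missing. Ten percent missing in both arms lowers power from 0.516 to 0.439. These sizes are illustrations, because the protocol states no cancellation rate. The change should be made: it is inexpensive and removes most of the problem at source.

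**What to change.** 1. Reconcile 10.1, Tables 1.3-2 and 7.5-2, and 7.5.3. Unless consent to data use is withdrawn, take vital status and oxygen or respiratory support at 36 weeks PMA from the NICU record for every infant in the FAS, including after cancellation before delivery. For infants born at 32 weeks or later, use the protocol's own assessment time. Derive BPD36 from these data and use it as observed in the main analysis.
2. For outcomes still missing, report beside the missing-as-event result an FAS analysis that does not score them as events, for example observed cases or multiple imputation. Show the number missing by arm and by reason for cancellation.
3. State that Phase III planning will use observed rates.

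The cost is a protocol amendment with the documented justification and committee review that 14.3 requires, a consent sentence on continued data use, and some chart abstraction. This edition is dated November 2023 and registration was planned to close in March 2024, so the change comes late in an open-label trial. It should be justified without reference to results by arm. Keeping the missing-as-event result in the report preserves the prespecified analysis. No visit, dose or clinical rule changes.

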### 5.2.2 REASONS FOR SETTING THE NUMBER OF CASES

In this study, since fetal and neonatal deaths were considered to be at higher risk of developing BPD and infant deaths up to 36 weeks PMA were also considered as one of events, infant deaths up to 36 weeks PMA (5%) were also taken into account to establish effect sizes for the two groups.

In a previous foreign study, the incidence of BPD36 was 26.4% (29/110, all children survived) when 110 pregnant women who developed pPROM at <28 weeks of gestation were treated with AZM. In a previous study in Japan, the incidence of BPD36 was 18.2% (2/11, all children survived) when 11 pregnant women with pPROM at <28 weeks of gestation were treated with ABPC/SBT + AZM. In addition, when ABPC/SBT + AZM was administered to 10 pregnant women with pPROM at <28 weeks of gestation from June 2013 to May 2020 at Saga Hospital, the incidence of BPD36 was 40.0% (4/10, all children survived) ([name] *et al*, unpublished data). Based on the above, the incidence of moderate or severe BPD36 or child death by 36 weeks PMA in the intervention group (AZM group) was assumed to be 18.0% to 40.0%.

On the other hand, the literature search did not retrieve any reports of EM administration to pregnant women with pPROM at <28 weeks' gestation alone. Therefore, we assumed that the incidence rate of moderate or severe BPD36 or infant death by 36 weeks PMA in the control group (EM group) was 60.0% based on the general BPD36 incidence rate.

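### The main analysis and the only p-value leave out the two factors that stratify randomisation; the crude analysis is valid, but its interval is slightly too wide if those factors are prognostic

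*Protocol*

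**What the plan says.** - **Randomisation (Protocol 4.2).** Allocation is 1:1 and stratified by pPROM onset (22w0d to 23w6d, or 24w0d to 27w6d) and by whether the facility uses early caffeine, which makes four strata. The reason given begins "Because the incidence of BPD varies with the number of weeks of gestation at the onset of pPROM" and covers the facility factor too; for that reason "stratification factors will be used at the time of randomization". Section 4.3 repeats the argument for gestational age.
- **Main analysis (14.2.2).** After the proportion in each arm: "In addition, the difference in proportions between groups and their 95% confidence intervals will be calculated. This will be the main analysis".
- **Test (14.2.2).** Two-sided at 0.05: "The p-value will be calculated by testing the difference in proportions". No stratification is named.
- **Adjusted analysis (14.2.2).** "The Mantel-Haenszel adjusted risk difference and its 95% confidence interval will also be calculated", over the same two factors. It has an interval, no p-value, and a place after the main analysis. The table in that section lists it second.
- **Power (5.2.2).** "Under a two-tailed test and a significance level of 5%, the power of detection ranged from 0.516 to 0.995" for intervention rates of 40% down to 18% against a control rate of 60%, with 50 per arm.

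**The concern.** The protocol calls two factors prognostic and randomises within them, then leaves them out of the estimate and test that decide the result. Stratified allocation balances the arms on those factors, so differences between strata contribute little to the sampling variation of the treatment difference. The crude standard error still counts that variation. If the factors are prognostic, the crude interval is therefore wider than the design warrants.

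The choice affects the headline. Two risk differences with slightly different intervals are prespecified, and they can fall on opposite sides of zero. At a stated power near one half for 60% versus 40%, a borderline result is a real possibility. Section 2.2 makes a phase III trial depend on what this one shows.

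**Working it through.** **1. Reproduce the stated power.** Inputs from 5.2: n = 50 per arm, control 60%, intervention 40% or 18%, two-sided 5%. For the unadjusted pooled z-test without continuity correction,

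power = Φ{ (d − 1.96·√(2·p̄(1−p̄)/n)) / √((p₁(1−p₁)+p₂(1−p₂))/n) }.

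- 60% vs 40%: (0.20 − 1.96 × 0.1000)/0.0980 = 0.041, so power is 0.516.
- 60% vs 18%: (0.42 − 1.96 × 0.0976)/0.0880 = 2.60, so power is 0.995.

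Both match. The stated power is that of the crude test, so 5.2.2 and the declared main analysis agree with each other.

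**2. Gestational contrast from the protocol's rates.** Section 2.1.1 gives BPD36 by week of delivery (22 to 30 weeks): 76, 72, 67, 58, 50, 41, 32, 24, 17%.

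- Taken at the week of onset: (76+72)/2 = 74% against (67+58+50+41)/4 = 54%, a contrast of 20 points.
- Shifted by the 2-week median latency in 5.2.2: (67+58)/2 = 62.5% against (50+41+32+24)/4 = 36.75%, a contrast of about 26 points.

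**3. Assumptions.** The protocol gives neither stratum sizes nor a caffeine effect. Assumed: early-onset stratum w = 20% to 50% of patients, caffeine contrast k = 0 to 10 points with a 50/50 split.

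**4. Effect of stratifying.** Between-stratum variance V_b = w(1−w)c² + 0.25k². Average outcome variance v = (0.60×0.40 + p(1−p))/2, which is 0.24 at p = 0.40. With f = 1 − V_b/v, the standard error shrinks by the factor √f and the effective sample is 50/f per arm. At 60% vs 40%:

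| w | c | k | V_b | √f | 50/f | power |
|---|---|---|---|---|---|---|
| 0.2 | 0.20 | 0 | 0.0064 | 0.987 | 51.4 | 0.527 |
| 0.3 | 0.20 | 0.10 | 0.0109 | 0.977 | 52.4 | 0.535 |
| 0.5 | 0.26 | 0.10 | 0.0194 | 0.959 | 54.4 | 0.551 |

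The standard error is 1.3% to 4.1% smaller, and power goes from 0.516 to between 0.527 and 0.551. Over the same assumptions, power goes from 0.936 to 0.942-0.955 at 60% vs 26.4%, and from 0.995 to 0.996-0.998 at 60% vs 18%. With a weak contrast (w = 0.2, c = 0.10, k = 0), power at 60% vs 40% is 0.519.

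**5. Simulation check.** 40,000 trials per scenario, N = 100, four strata, blocks of 4 (assumed), 60% vs 40%, early stratum 30%:

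| c | k | crude power | CMH power | MH Wald power | MH/crude width |
|---|---|---|---|---|---|
| 0.10 | 0 | 0.541 | 0.528 | 0.542 | 0.996 |
| 0.20 | 0.10 | 0.542 | 0.539 | 0.555 | 0.977 |
| 0.30 | 0.10 | 0.542 | 0.556 | 0.574 | 0.954 |

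Simulated crude power is near 0.54 rather than 0.516 because the outcome is discrete: summing the two binomial(50) distributions exactly over the rejection region gives 0.543. Methods should therefore be compared within the table. Over all scenarios run, the MH Wald test gained 0 to about 3 points on the crude test. CMH (the Cochran-Mantel-Haenszel test) ranged from about 1.6 points below it to about 1.4 above.

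**6. Type I error.** Crude: 0.058 with no stratum contrast, 0.052-0.053 at 20 points, 0.047 at 30 and 0.040 at 40. CMH: 0.049-0.054. MH Wald: 0.054-0.058.

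**The case against.** The strongest reply is that nothing here is invalid. The crude test holds up under stratified randomisation, it is the test the trial was powered on, and the adjusted estimate with its interval will be reported in any case. A phase II trial meant to size phase III also needs crude arm proportions. Section 14.3 requires documented review, a protocol revision and an ethics committee opinion before such a change. This edition is dated November 2023, with enrolment planned to close in March 2024 (7.6), so changing the main estimator late in an open-label trial has a credibility cost.

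All of that stands, and it limits the point to a modest one. It does not supply a reason for leaving the design factors out of the main analysis.

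Three stronger readings are tempting and are not supported:

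- **That the crude analysis is miscalibrated.** At the 20-point contrast its type I error was 0.052-0.053. It fell clearly below 0.05 only at contrasts of 30 to 40 points, beyond the 20 to 26 that the protocol's rates imply.
- **That the omission explains the low power.** The 0.516 comes from N = 100, set for feasibility. Stratifying adds at most about 3.5 points under the assumptions above.
- **That any stratified test is a free gain.** With weak strata CMH loses a point or more.

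**Conclusion.** The point holds as a matter of consistency between design and analysis, with a small gain in precision. The protocol treats both factors as prognostic and randomises on them, but its headline estimate, interval and p-value ignore them. With the protocol's gestational contrast of 20 to 26 points, the crude standard error is about 1-4% too large and about 1 to 3 points of power are forgone at 60% vs 40% (3.5 at the edge of the assumed range). At larger effects the loss is smaller, and with weak strata it is nil. The size rests on assumed stratum sizes, an assumed caffeine contrast of 0 to 10 points, and delivery-week rates standing in for onset-week rates. The direction does not depend on those values, provided that the factors are prognostic as the protocol says.

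**What to change.** 1. In 14.2.2, make the Mantel-Haenszel risk difference with its 95% CI over the four randomisation strata the main analysis.
2. Name one stratified test for the primary p-value in advance. CMH holds its level but may gain or lose about 1.5 points of power against the crude test. The MH Wald test agrees with the interval and gains 0 to 3 points, but runs slightly above 5%. If CMH is chosen, say which result governs should it disagree with the interval.
3. Keep the crude difference and the arm-level proportions as supportive results and as inputs for sizing phase III.
4. In 5.2.2, note that the stated 0.516 to 0.995 is the power of the unadjusted test.

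**Cost.** No new data and no new estimator, since both estimates are already planned. It does need a documented protocol revision with ethics committee opinion under 14.3, made before the data are unblinded for analysis. The benefit is a small efficiency gain and a main analysis that follows the randomisation.
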